### Adverse events

Participants might experience fatigue while doing exercise, and therefore adequate rest periods and breaks will be provided as needed. Vital signs will be constantly monitored before, during and after the interventions every session. Light refreshments will be provided to prevent dehydration. In some activities that will challenge their balance, trained therapists will be close by to provide support to prevent them from falling. The calendar-diary will also be used to monitor changes in health status and record adverse events every session during the intervention period and then every month after the intervention phase. In the case of any untoward incident like dizziness, injuries, or falls during the conduct of the study, appropriate first aid, medical attention or referral to a clinic or hospital, will be immediately done to the participant as soon as reported.

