### Study design and procedures

This proposed study is a randomized controlled trial using a 4-group design including three intervention groups (physical training alone or cognitive training alone, or combined physical and cognitive training) and one waitlist control group. The study will comply with the principles of the Declaration of Helsinki 2013 and Good Clinical Practice Guidelines. Ethics approval was secured from the Human Subjects Ethics Sub-committee of the Hong Kong Polytechnic University-Department of Rehabilitation Sciences (HSEARS20170402001) and the Ethics Review Committee of the University of Santo Tomas-College of Rehabilitation Sciences (FI-2017-002). The SPIRIT guidelines were followed in the design of this study protocol.

Trained study personnel will interview the participants using questionnaires to obtain their demographic information and medical history, physical activity level and history of falls, and will conduct cognitive and physical performance tests to determine their eligibility to participate in this study. Only those who signed the informed consent will be included in this study.

Random allocation will be carried out by a third party not involved in the study by random draw to blindly allocate each participant to one of the four groups. To minimize experimental contamination through social interaction and communication among the participants, the interventions will be delivered at different sites.

Measurement points include baseline/pre-intervention, post-intervention, and six months follow-up assessments and will be conducted by trained study personnel blinded to the randomization assignment. Physiotherapists and occupational therapists who will be administering the interventions will not be involved in the outcome assessment. They will also have workshops and discussions to standardize the administration of the different training programs. After the intervention period, aside from a calendar-diary, monthly phone calls will also be done to follow up the participants about their fall status, physical activity, and exercise behavior. Figure 1 illustrates the study flow. Appendix shows the timeline of the study.

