### Outcomes measures

The following primary and secondary outcome measures will be performed by trained assessors blinded to the group allocation. Measurements will be taken at baseline, at the conclusion of the intervention period, and 6 months post-intervention. Additional information regarding the exercise behavior and the physical and social activities participated in by the eligible participants in the last 6 months will be obtained during the 6 months post-intervention follow-up assessments [52].

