### Primary outcome measure

#### Falls rate

Each participant will be given a calendar diary to mark any incidence of fall on a weekly basis during the assessment period. A relative or caretaker of the older person will be asked to validate the information. The confirmation by another person is done because self-reporting techniques, particularly for individuals with cognitive impairment, may not be accurate due to recall bias [53]. Monthly phone calls will be done to update the falls history of each participant.

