#### Overall fall risk

The overall fall risk will be determined using the short-form Physiological Profile Assessment (PPA) and the Falls Risks for Older People in the Community (FROP-Com) Screen.

The PPA short form is a valid, reliable and objective series of tests used to evaluate the physiologic risks of falls and to classify fallers from non-fallers [54]. It is composed of five subtests on 1) visual contrast sensitivity, 2) proprioception, 3) hand reaction time, 4) knee extensor muscle strength, and 5) postural sway [55]. Data from these tests will be encoded in a web-based software program such that the performance of one participant is compared to a normative database to determine whether the individual has a low or high risk of falls [55].

The FROP-Com Screen is a brief screening tool used to determine older persons who are prone to fall [56]. It is composed of three items on 1) the number of incurred falls within the past 12 months, 2) the level of dependence in doing instrumental ADLs, and 3) balance in walking and turning of older adults [56]. A score of 0–3 means the older adult has a low risk for falls, while a score from 4 to 9 denotes a high risk for falls [56].

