### Statistical analysis

Descriptive statistics will be used to summarize demographic data using mean standard deviations, and percentages. Baseline values across the groups will be compared using one-way ANOVA for interval/ratio data and Kruskal-Wallis test for nominal/ordinal data. The multivariate repeated measure ANOVA will be used to determine the pre- and post-intervention effects and differences among group data with a normal distribution; otherwise the Friedman test will be utilized. The incidence rate ratio, computed as the number of falls divided by the duration of falls monitoring for every participant, will be used to compare intergroup fall rate. An intention-to-treat analysis will be used for missing data due to dropouts. The *p*-value of < 0.05 is considered significant. Data analysis will be performed using SPSS version 23 for Windows.

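### In weeks 1–12 the falls diary is used at every training session, but the waitlist may have no scheduled staff contact about falls, so its falls may be captured slightly less completely

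*Protocol article*

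**What the plan says.** The primary outcome is the falls rate. The Falls rate section of the Protocol article sets up the same basic recording in every arm: "Each participant will be given a calendar diary to mark any incidence of fall on a weekly basis during the assessment period". A family member or carer is asked to confirm the entries, because "self-reporting techniques, particularly for individuals with cognitive impairment, may not be accurate due to recall bias". The section adds: "Monthly phone calls will be done to update the falls history of each participant". It gives no start for these calls.

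Two other sections bear on weeks 1–12:

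- Study design and procedures dates the calls: "After the intervention period, aside from a calendar-diary, monthly phone calls will also be done to follow up the participants about their fall status".
- Adverse events gives the same diary a safety role: "The calendar-diary will also be used to monitor changes in health status and record adverse events every session during the intervention period". After the intervention this use becomes monthly. Falls are named there among the incidents that call for first aid or referral.

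The Interventions section sets three sessions a week for 12 weeks in PT and PACT and one a week for 12 weeks in CT. The waitlist keeps its normal routine and receives PACT later, at a time that is not given.

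All arms have blinded assessments: "Measurements will be taken at baseline, at the conclusion of the intervention period, and 6 months post-intervention". One item of the FROP-Com Screen asks for "the number of incurred falls within the past 12 months". Statistical analysis bases the between-group comparison on a rate "computed as the number of falls divided by the duration of falls monitoring for every participant".

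**The concern.** A falls rate is only comparable between arms if falls are found equally well in each. Here the diary that yields the primary outcome is also opened at training sessions, and the waitlist has none. If the common calls start only after the intervention, the waitlist has no stated staff contact about falls between baseline and the post-intervention assessment. These are people whose unaided reports the protocol itself regards as possibly inaccurate.

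If session contact prompts fuller diary entries, a trained arm would record more falls than the waitlist at the same true rate, and a real benefit of training over no training would look smaller. The protocol projects such a benefit in its abstract. The error would be systematic, so a larger sample would not reduce it.

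**Working it through.** **Sessions in weeks 1–12** (Interventions section)

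- PT: 3 × 12 = 36
- PACT: 3 × 12 = 36
- CT: 1 × 12 = 12
- Waitlist: 0

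**Which comparisons are exposed**

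- PACT versus PT: 36 against 36, so no difference.
- PACT versus CT: 36 against 12. The diary is marked weekly and CT meets weekly, so each diary week in CT already has a session. Little or no difference is expected.
- PT, CT or PACT versus waitlist: 36, 12 or 36 against 0. This is where a difference can arise.

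**Share of the monitored time.** If monitoring starts at randomisation, it lasts 12 weeks plus 6 months (26 weeks), or 38 weeks. Weeks 1–12 are 12/38 = 0.316 of it. Taking nine months from the Appendix timeline as 39 weeks gives 12/39 = 0.308.

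**Illustration of size.** The document gives no capture rate, so these are assumptions. Let 0.90 of falls be captured in a trained arm throughout and in the waitlist after week 12. Let waitlist capture be lower by g in weeks 1–12. With equal true rates, the recorded ratio (trained to waitlist) is

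(38 × 0.90) / (12 × (0.90 − g) + 26 × 0.90)

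| g | Recorded ratio | Log | True 0.70 recorded as |
|---|---|---|---|
| 0 | 34.2/34.2 = 1.000 | 0 | 0.700 |
| 0.05 | 34.2/33.6 = 1.018 | 0.018 | 0.713 |
| 0.10 | 34.2/33.0 = 1.036 | 0.036 | 0.725 |
| 0.20 | 34.2/31.8 = 1.075 | 0.073 | 0.753 |

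With 39 weeks, and full capture except in the waitlist in weeks 1–12, the factors for gaps of 0.05, 0.10 and 0.20 are 1.02, 1.03 and 1.07, so the result does not depend on these choices.

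**Against sampling error.** With 23 per arm (Sample size computation), person-years per arm are 23 × 38/52 = 16.8. At an assumed 1 fall per person-year in both arms and Poisson variation, the standard error of the log rate ratio is √(2/16.8) = 0.345. It is 0.282 at 1.5 falls and 0.488 at 0.5 falls per person-year. The shift is 0.018/0.345 = 5% of one standard error at g = 0.05 and 0.073/0.345 = 21% at g = 0.20.

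**The case against.** The case against making much of this is strong, and most of it stands.

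- **The core recording is common to all arms.** The weekly diary, confirmation by a second person and the blinded assessments cover the waitlist too. The remark about recall is the protocol's reason for that confirmation. The FROP-Com item is a further recall check in every arm, although at the post-intervention visit it also spans about 12 − 3 = 9 months before the intervention. A reader might infer that waitlist falls go unrecorded in weeks 1–12. The documents do not support that.
- **The mechanism is inferred.** The session use of the diary is described for health changes and adverse events. Nothing says that therapists go through earlier fall entries or that session entries feed the primary count.
- **The calls may already run throughout.** The Falls rate section does not confine them to the later period. If they run from the start, the gap shrinks. If weeks 1–12 do not count towards the rate, it disappears.
- **The main hypothesis is barely touched.** The Background sets PACT against physical or cognitive training alone. A reader might infer from 36 against 12 sessions that PACT versus CT is distorted. The weekly CT session matches the weekly diary mark, and the document gives no reason why three contacts per mark should find materially more falls than one.
- **The effect is small and runs against training.** It cannot create a false claim of benefit. The standard error used above is also optimistic: the protocol expects 16% dropout, and with 20 per arm the standard error is about 0.37. Overdispersion would raise it further.

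What survives is narrow. Two sections of the protocol differ on when the calls apply, and on the reading in Study design and procedures the waitlist alone lacks scheduled contact about falls in weeks 1–12. Exact call dates could be left to a fuller protocol, but here the article states a start in one place and none in the other.

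**Conclusion.** The point holds as a modest one. As written, falls in weeks 1–12 may be captured slightly less completely in the waitlist than in the training arms, which would lean the training-versus-waitlist comparisons against training. PACT versus CT is affected little if at all, and PACT versus PT not at all.

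The conclusion rests on three conditions: the calls start after the intervention, weeks 1–12 count in the rate, and session contact improves diary completeness. The document states the first in one section, leaves the second open and is silent on the third. The size therefore cannot be derived from it. Under the assumed gaps of 0 to 0.20 the recorded ratio is inflated by a factor of 1.00 to 1.08, probably well below one standard error. This is a worthwhile low-cost improvement and not a flaw that decides the result.

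**What to change.** Amend Study design and procedures to agree with the Falls rate section: monthly fall-status calls run from randomisation in all four arms, are made by staff blinded to allocation, and follow one diary-return schedule. Record the source of every fall (diary, call or session) and keep all falls in the primary count, so that falls known only from sessions can be seen by arm.

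The cost is about 3 extra calls per participant in months 1–3, or 3 × 93 = 279 calls through a channel the trial already runs, plus one data field. Session contact stays unequal, so the change reduces the difference without removing it.

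An analysis restricted to the 6 months after the intervention can serve as a check, but only if the waitlist does not start its PACT programme within that window. The protocol should say when that programme starts. This analysis is less precise: 23 × 26/52 = 11.5 person-years per arm gives a standard error of √(2/11.5) = 0.417, which is 21% larger than 0.345. It should not replace the primary analysis. If the calls can no longer be changed, this check needs only dated fall entries.

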### Interventions

#### Physical training alone (PT)

The participants in the PT group will be performing a series of physical exercises as a group supervised by trained physiotherapists. To ensure proper guidance and safety in the performance of the exercises, there will be one physiotherapist for every five participants.

The exercise program will start with 5–10 min of warm-up including calisthenics and general flexibility exercises, followed by 60–90 min of multicomponent exercise programme including endurance, strength and balance exercises (with a focus on balance training), and will end with 5–10 min of cool down including calisthenics and general flexibility exercises. This will be done three times per week over 12 weeks to achieve the recommended minimum accumulated 40 h of exercise [13]. The exercises will be progressed individually, increasing the repetitions or sets first before the resistance, to maintain a moderate level of exercise intensity which is 5 to 6 on a scale of 0 to10 for the level of physical exertion [47]. Rest periods will be provided whenever necessary. Table 1 shows the types of exercises included in this program.

**Table 1 Tab1:** Physical training program

Periods	Exercises	Progression
Warm-up (5–10 min)	Calisthenics and general flexibility	
Multicomponent exercise programme (60–90 min)	Walking over 10 m 1. Walking forward-backward, sideways 2. Turning figure of 8 walking 3. Tandem walking	10–12 rounds; 1–3 sets Increase step length and speed Over obstacles
	Sit-to-stand	8–12 repetitions; 1–3 sets Lower chair height
	Heel and toe raises	8–12 repetitions; 1–3 sets Hold or raise for longer
	Stepping in different directions	8–12 repetitions; 1–3 sets Longer or faster steps Step over obstacle
	Step-ups 1. Forward 2. 2. Lateral	8–12 repetitions; 1–3 sets Increase step height
	Graded reaching in standing 1. Table top - side to side, forward and diagonal reaching 2. Tapping markers on the wall 3. 3. Reaching down to chair, stool or floor	8–12 repetitions; 1–3 sets Narrower foot placement Increase distance to reach Standing on a softer surface (rubber mat) Stepping while reaching
Cool-down (5–10 min)	Calisthenics and general flexibility	

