#### Cognitive training alone (CT)

The participants in the CT group will be involved in a set of paper-based cognitive exercises as a group supervised by trained occupational therapists. To provide close monitoring and immediate feedback during the training, there will be one occupational therapist for every five participants.

The intervention will start with 5–10 min of warm up to give the instructions, followed by 60–90 min of cognitive training designed to train specific cognitive functions such as orientation, memory, attention and executive function, with emphasis on executive function which is associated with increased risk for falls in older adults [25], and will end with 5–10 min of cool down for feedback and processing of responses. This will be done once a week for 12 weeks which is the optimal duration of cognitive training [30]. Even though the cognitive training is delivered in a group, the difficulty level and progression will be individualized. Rest periods will be provided whenever necessary.

Table 2 shows the contents of the cognitive training. The contents of training for orientation and attention were based from Brum et al. (2009) [49], and Vojtkofsky and Feldman (2015) [50]. For memory, training will include rehearsal, association, visual imagery and concentration. The use of multiple strategies in memory training is chosen as larger improvement is expected with this approach compared to single strategy approaches [50, 51]. For executive function, training will consist of extensive repeated practice of practical tasks to simulate usual daily activities instead of relying on strategies to strengthen cognitive processes. This is founded on the process-based approach which has been proven to be highly effective in improving executive function [27].

**Table 2 Tab2:** Cognitive Training program

Periods	Components	Content
Warm-up (5–10 min)	Giving of instructions	
Cognitive training (60–90 min)	Orientation training	Orientation to person, place, and time with or without external cues like newspaper, calendar a. person – give full name, relatives, neighbors, age, occupation; name public officials b. place – provide address, location of islands/cities/provinces, favorite place/destination c. time – determine current time, day, month and year; schedule of TV shows; special occasions; weather, season

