#### Physical and cognitive training (PACT)

The participants in the PACT group will be performing activities that integrate cognitive training in physical exercise routines as a group supervised by trained personnel either physiotherapists or occupational therapists. To ensure proper guidance, safety, close monitoring and immediate feedback about their performance of the activities, every five participants will be supervised by one therapist.

The PACT programme will start with 5–10 min of warm-up including calisthenics and general flexibility exercises, followed by 60–90 min of exercises similar in design, intensity and progression with the PT group but with cognitive components incorporated in each type of exercise, and will end with 5–10 min of cool down including calisthenics and general flexibility exercises and a post-session discussion to recall the activities performed in the just-concluded session. This will also be done three times per week over 12 weeks. Rest periods will be provided whenever necessary. Table 3 presents the design of the PACT program. The participants will likewise be given the same brochures given to the PT and CT groups for additional information and reference.

**Table 3 Tab3:** Physical and cognitive training program

Periods	Exercises	Progression
Warm-up (5–10 min)	Calisthenics and general flexibility	
Multicomponent exercise programme (60–90 min)	Walking with executive function training • From a mixed set of objects (30 pieces) on a table at the start of the line, bring one object at a time walking over 10 m towards another table to sort the objects properly in 3–4 separate groups. Walking is done forward, backward, sideward, in figure of 8, or tandem.	10–12 rounds; 1–3 sets Increase step length and speed Walking over obstacles
	Sit-to-stand with orientation training • Stand every time to answer questions about orientation to person, place and time	8–12 repetitions; 1–3 sets Lower chair height
	Heel and toe raises with attention training • Follow visual cues to do heel or toe raises	8–12 repetitions; 1–3 sets Hold or raise for longer
	Stepping in different directions with memory training • Stepping on a set of specified number and sequence of markers on the floor	8–12 repetitions; 1–3 sets Longer or faster steps
	Step-ups with attention training • Follow verbal instructions on which foot to use to step-up	8–12 repetitions; 1–3 sets Increase step height

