#### Waitlist group (WG)

The participants in the WG will serve as the control group on waitlist. They will be instructed to go on with their usual daily routine and will receive the intervention, combined physical and cognitive training, at a later date.

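### In the 12-week intervention period, scheduled adverse-event recording follows training sessions (36 in PT and PACT, 12 in CT, none in the waitlist group), so by-arm counts would mix harm with opportunity to record

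*Protocol article*

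**What the plan says.** The Adverse events section gives the calendar-diary a second use besides falls: to follow changes in health status and to "record adverse events every session during the intervention period and then every month after the intervention phase". The recording occasion in the first phase is thus the training session.

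The Interventions section sets the number of sessions:

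- PT: "This will be done three times per week over 12 weeks".
- PACT: "This will also be done three times per week over 12 weeks".
- CT: "This will be done once a week for 12 weeks".
- Waitlist group: no sessions. "They will be instructed to go on with their usual daily routine", with the combined training offered later.

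Two other provisions reach every arm, but neither names adverse events. Under Falls rate, each participant holds a calendar diary and marks falls weekly, with confirmation by a relative or caretaker. The monthly telephone calls concern falls history (Falls rate) and, after the intervention, fall status, physical activity and exercise behaviour (Study design and procedures).

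**The concern.** Where the treatment schedule also sets how often adverse events are recorded, arms with more contact have more chances to enter an event. PT and PACT participants meet a therapist three times a week, CT participants once, and waitlist participants never. Dizziness, pain or a minor injury of the kind older adults report in any 12 weeks would have many more scheduled chances of being written down in the exercise arms.

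What is at stake is the reading of any table of adverse events by arm for the training period. A higher count under PT or PACT could reflect harm from exercise, more frequent recording, or both, and the table could not separate them. The waitlist group is the only arm that could show the background rate of such complaints over the same weeks, and it has no scheduled record then.

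This is separate from how falls are ascertained. Making falls reporting more even across arms would leave the session-based rule for all other events as it stands.

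**Working it through.** The article states no count of recording occasions, so there is no figure to reproduce. The count follows from its own schedule.

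**Inputs.** Sessions per week: 3 (PT), 3 (PACT), 1 (CT), 0 (waitlist), from the four Interventions subsections. Duration: 12 weeks, or 12 × 7 = 84 days. Recording rule: once per session, then monthly (Adverse events). Follow-up after the intervention: 6 months (Outcomes measures). One reading is assumed: the waitlist group's deferred training starts after the 12 weeks, since the article gives it no date.

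**Occasions during the intervention** = sessions per week × 12. **Mean interval** = 84 ÷ occasions. **Whole study** = occasions during the intervention + 6 monthly records.

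| Arm | Occasions in 12 weeks | Mean interval | With 6 monthly records |
|---|---|---|---|
| PT | 3 × 12 = 36 | 84/36 = 2.33 days | 42 |
| PACT | 3 × 12 = 36 | 84/36 = 2.33 days | 42 |
| CT | 1 × 12 = 12 | 84/12 = 7 days | 18 |
| Waitlist | 0 × 12 = 0 | none | 6 |

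The exercise arms have 36/12 = 3 times the scheduled occasions of CT. No ratio to the waitlist group exists. The whole imbalance arises in the first 12 weeks, because the monthly phase adds the same 6 to each arm.

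**Could another provision fill the gap?** The weekly diary rule covers falls. The monthly calls cover falls, physical activity and exercise behaviour. The closing sentence of the Adverse events section promises care once an untoward incident is reported, in any arm, but sets no occasion for reporting. None of these gives the waitlist group a scheduled adverse-event record during the 12 weeks.

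**With one weekly entry in every arm**, the 12-week counts become 1 × 12 = 12 in each of the four arms, in place of 36, 36, 12 and 0.

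**The case against.** The strongest reply is that the Adverse events section is about participant safety and not about comparing arms. Adverse events are not among the outcomes, and Statistical analysis gives no analysis of them. Checking people whenever they exercise is a reasonable safety rule. Waitlist participants hold the same diary, nothing bars them from noting other events, and an article may leave the interval for them to the full protocol.

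Much of this stands. No formal harms comparison is planned, so no stated analysis is invalid, and actual recording in the waitlist group may exceed zero. What does not stand is the appeal to condensation. The article is not silent on timing: it states a schedule, and that schedule depends on the arm.

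Three stronger readings are tempting, and the document supports none of them.

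- *Harms cannot be compared between arms at all.* Recording is monthly in every arm for about six months after the intervention, and falls are marked weekly in every arm throughout.
- *Events in the waitlist group would go unnoticed for 12 weeks.* Falls marking, unprompted diary entries and the post-intervention assessment all give some chance of learning of them.
- *The exercise arms would show three times as many events as CT at equal true rates.* Three is the ratio of occasions. Suppose an event is captured only if it occurred within D days before a session. The captured share is then min(1, D ÷ interval), which for PT or PACT against CT gives 43% against 14% at D = 1, 86% against 29% at D = 2, 100% against 43% at D = 3, and 100% against 100% at D = 7. The ratio runs from 3.0 down to 1.0, so it depends wholly on D. The article gives no D, and a written diary entry need not lapse before the next session.

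**Conclusion.** The point holds for the 12-week intervention period only. Scheduled adverse-event recording is 36, 36, 12 and 0 occasions in PT, PACT, CT and the waitlist group. By-arm counts for that period, even purely descriptive ones, would mix true harm with opportunity to record, and there would be no scheduled concurrent control rate.

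The counts rest on the stated session frequencies and on the waitlist group having no training in those weeks. How far event counts would be distorted cannot be computed from the document, because that depends on how completely participants write down events between sessions and without prompting. The primary falls outcome and the monthly recording phase are not affected. This is a worthwhile, inexpensive improvement to data collection. It does not invalidate any planned analysis.

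**What to change.** In the Adverse events section, separate the comparative record from session safety recording.

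1. From allocation to the end of the intervention, participants in all four arms make the same weekly adverse-event entry, with the same questions, in the calendar-diary each already holds.
2. From then to the 6-month assessment, the same monthly recording applies in all four arms.
3. Session-based safety recording continues as now, but those events are logged separately and reported descriptively within arm. They are not used to compare arms.

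The cost is a change of wording and a short added section in an existing diary. The downside is slightly more diary burden, mainly for the waitlist group. Session safety procedures and clinical care do not change.
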